## Abstract

**Background:**

School safety is fundamental to fostering positive outcomes for children. Violence remains a critical public health issue with 8.1% of elementary and 21.8% of middle school students reporting daily or weekly bullying in 2015–16. Similarly, over half of lifetime mental health concerns become evident before age 14. Thus, elementary school is a key time for comprehensive school safety interventions. Yet, interventions are rarely delivered with fidelity in community settings. Evidence-based interventions must be complemented by implementation strategies to achieve desired public health outcomes.

**Methods:**

We develop and test an intervention focused on promoting a positive school climate guided by a school-based 3-person leadership team (3-PLT) using a hybrid Type II design. The 3-PLT includes a School Resource Officer, (SRO), administrator and mental health services professional as a newly appointed climate specialist (CS). The interventions to be delivered include 1) Restorative justice, 2) Mental Health First Aid and 3) Crime Prevention Through Environmental Design. The CS will lead the team and coordinate implementation through a process of interactive problem solving and supports, consistent with the implementation facilitation strategy. We will conduct a cluster randomized controlled trial with staged entry over two school years in Genesee County, Michigan (*n* = 20 elementary schools, with 10 participating per school year). We will use a combination of data sources including data collected by schools (e.g., discipline data), a student survey, and a teacher survey. We will also conduct a process evaluation and assess implementation and sustainability through focus groups with key stakeholders, teachers, and students. Finally, we will conduct a cost-benefit analysis.

**Discussion:**

Results from both the behavioral outcome and implementation strategy evaluations are expected to have significant implications for school safety and student well-being. This study adopts a unique approach by integrating three evidence-based programs and incorporating implementation facilitation led by the CS as part of the 3-PLT to support intervention delivery and enhance public health impact among schools in disadvantaged communities with students at risk of poor health outcomes. This study aims to create a comprehensive, well-integrated model intervention that is sustainable and can be translated to similar high-risk settings.

**Trial registration:**

Trial was retrospectively registered, registration ISRCTN1226421, May 16, 2019.

## Background

School safety is fundamental to fostering positive short and long-term outcomes for children, including positive mental health, school connectedness, student retention and academic success (Battistich, Schaps, & Wilson, 2003; Horner et al., 2009). We define a safe school as one that minimizes violence, promotes student mental health, and fosters a social climate that promotes positive development. Unfortunately, concerning rates of school violence persist in the US: in 2017, 19.0% of students were bullied, 15.7% carried a weapon at least once in a month (3.8% on school property), and 6% had been threatened or injured with a weapon (Kann et al., 2018). Rates of violent, aggressive, and bullying behaviors are similarly concerning among younger students with 8.1% of elementary and 21.8% of middle school students reporting daily or weekly bullying in 2015–16 (Diliberti, Jackson, & Kemp, 2017). Violence victimization is associated with distress, adjustment difficulties, and mental health problems. Exposure to violence, including direct victimization and well as exposure in the school environment, is a potent risk factor for poor mental health outcomes including depression and anxiety (Kennedy, Bybee, Sullivan, & Greeson, 2010).

The CDC (Perou et al., 2013) identifies mental health problems, including depression and anxiety, as a critical public health issue among youth with significant impact on the individual, family, and community. Mental health issues that go untreated early in life are associated with further problems, including increased likelihood of academic failure, dropout, substance use, relationship conflicts, violence, and suicide (World Health Organization, 2012). In the short term, mental health problems evident in middle school predicts school absences a year later (Suldo, Thalji, & Ferron, 2011). In addition, many children, particularly those living in low resource communities, experience disproportionate risk of violence and subsequent mental health consequences without sufficient treatment and prevention services needed to reduce risk of poor outcomes (O’Connell, Boat, & Warner, 2009). Childhood vulnerability is exacerbated in high stress environments when children and youth receive limited support from adults (O’Connell et al., 2009). Yearly, an estimated 13–20% of children aged 3–17 years experience a mental disorder, and more than half of lifetime psychiatric diagnoses have an initial age of onset before age 14 (Kessler et al., 2005).

School climate plays a major role in shaping the lives of students, affecting violence (Brookmeyer, Fanti, & Henrich, 2006), mental health and wellness (Jacobson & Rowe, 1999), truancy and achievement (Astor, Guerra, & Van Acker, 2010). The National School Climate Council recommends an encompassing definition of school climate that includes experiences of school life, that reflect the norms, goals, values, teaching, organization structure, and relationships. Relationships include connections among students, teachers, and staff; feelings of commitment to the institution; and connection to a community (Pittman & Richmond, 2007).

The relationship between student outcomes and school climate are evident longitudinally (Anderman, 2002; Goodman, 1997). Researchers have found that poor school-based relationships were associated with initiation of deviant behavior (Dornbusch, Erickson, Laird, & Wong, 2001; McNeely & Falci, 2004). Consequently, promoting a positive school climate is an important mechanism by which interventions can reduce risk of poor health outcomes including violence and mental distress. Researchers suggest that schools, particularly those with concentrated poverty, may benefit from multicomponent prevention approaches that improve positive discipline management and support positive psychosocial climates, effectively identify youth experiencing mental distress and improves the physical as well as social environment (Gottfredson, Gottfredson, Payne, & Gottfredson, 2005).

In order to effectively address challenging issues such as school safety, communities need to deliver multicomponent interventions targeting prevention efforts across levels of social ecology (Komro, Flay, Biglan, & Wagenaar, 2016; PriCowan, Vaillancourt, Rossen, & Pollitt, 2013). Even the best individual interventions have relatively limited scope in terms of outcomes when offered alone, and, consequently, small effects when taken to scale; therefore, multicomponent interventions have greater potential to achieve positive outcomes at the school or community level than a single intervention alone (Komro et al., 2016). Evidence-based interventions (EBIs) that address the multifaceted nature of school safety such as Restorative Justice (RJ), Mental Health First Aid (MHFA) and Crime Prevention Through Environmental Design (CPTED) when deloyed as a single, coordinated, multicomponent intervention approach, are promising approaches to improving the school environment.

Yet, more complex, multicomponent interventions are also more challenging to implement. Such interventions require effective implementation strategies to adopt the constellation of EBIs and adapt them to suit the needs of the context, providers and target population. Interventions will fail to achieve their desired effects if not implemented well (Durlak, 2015). Researchers have acknowledged that evidence-based interventions must be complemented by implementation strategies to achieve desired public health outcomes (Kirchner, Waltz, Powell, Smith, & Proctor, 2018). Implementation strategies are highly specified, theory-based methods to enhance EBI delivery in community settings and are key to bridging the research-to-practice gap (Kilbourne et al., 2014). Study designs that assess implementation strategy utility *and* evaluate EBI effectiveness, such as with hybrid designs, provide vital information for stakeholders about using implementation strategies with new innovations to maximize public health impact.

To inform the optimal implementation strategies for these effective interventions, we develop and test an intervention focused on promoting a positive school climate guided by a school-based 3-person leadership team (3-PLT) using a hybrid Type II design. A hybrid Type II design tests the effectiveness of the intervention and determines the feasibility and potential utility of an implementation strategy (Curran, Bauer, Mittman, Pyne, & Stetler, 2012). The 3-PLT includes representatives from the police (School Resource Officer, SRO), school (e.g., administration), and mental health services (i.e., social work), the latter of whom leads the team as a newly appointed climate specialist (CS). The team, led by the CS, work together to support the integration of the key intervention components: (1) RJ practices, (2) MHFA training, and (3) CPTED (see Fig. 1). The CS coordinates these efforts as a staff member within the school through a process of interactive problem solving and supports, consistent with the implementation facilitation strategy (Ritchie, Dollar, Kearney, & Kirchner, 2014). We will focus on change among students in an early developmental period—elementary school students aged 8–12 years—in a county with significant social and economic challenges. The purpose of this research is to study the effectiveness and implementation of three complementary interventions delivered concurrently to enhance school safety through improved school climate. School climate represents a critical mechanism by which interventions, including multicomponent school safety and mental health interventions, can reduce risk of violence and mental distress among youth.

**Fig. 1 Fig1:**
[figure not shown]
Proposed Conceptual Relationship Between Evidence-Based Interventions, Implementation Strategies and Study Outcomes. Adapted from Proctor et al. (2009) and Lyon (Lyon, 2018)

## Methods/design

### Aims and objectives

The overarching objective of this study is to provide a safe school environment to positively impact health, wellbeing, social, educational, violence and delinquency outcomes among youth. This is accomplished through the concurrent delivery of a multicomponent approach consisting of 3 integrated interventions: Restorative Justice (RJ), Mental Health First Aid (MHFA) and Crime Prevention Through Environmental Design (CPTED). The implementation strategy used is a facilitation approach based on the Implementation Facilitation, Enhanced REP, and the iPARiHS framework (Kilbourne et al., 2013; Ritchie et al., 2014) as part of the 3-PLT (see Fig. 1). Elementary school safety is understudied yet represents a critical period in which to develop positive mental health, build constructive and trusting relationships with adults, and prevent early experiences of violence.

### Primary study aim

The primary study aim is to examine the overall effectiveness of the intervention, including change in violence (e.g., fights, bullying, victimization), over time compared with a control group of students who receive school practice as usual.

### Secondary study aim 1

Employ implementation facilitation from an appointed school climate specialist (CS) to support delivery of a multicomponent, integrated intervention and evaluate feasibility and potential utility to support sustainment.

### Secondary study aim 2

Examine specific mechanisms associated with change in mental health (e.g., anxiety, depression, well-being), including perceptions of school climate as a moderator.

### Secondary study aim 3

Estimate the costs of the intervention and its implementation and conduct a cost-benefit analysis for positive outcomes, such as improve school climate perceptions, associated with participation in the interventions.

### Methods

The cluster randomized trial evaluates a school safety intervention in a community with significant need, Genesee County, Michigan (see Fig. 2). This study was reviewed and approved by the Michigan State University Institutional Review Board (IRB# × 15-1129e). This study takes advantage of ongoing partnerships with the Genesee Intermediate School District in Michigan. We do not intend to collect data from participants who discontinue or deviate from protocols. Among the primary data sources to be collected (e.g., focus groups, interviews, teacher surveys), the data will be kept on a password protected server and de-identified. The study does not employ a data monitoring committee, but this study is structured such that the intervention team (i.e., employees of the GISD), is separate from the training team (i.e., employees of international and regional organizations, local universities, and the district wide [GISD] training team offering training in facets of the intervention), which is separate from the data collection team (i.e., employees of the two universities charged with the process and outcome evaluation, led by a co-PI), which is separate from the data analysis team (i.e., employees of the two universities charged with the process and outcome evaluation, led by a separate co-PI), providing sufficient independence and protecting against potential conflicts of interest. Thus, those tasked with training and technical assistance associated with components of the intervention are not involved in the analysis of data or reporting of outcomes given the potential bias this might engender as a result of the incentives associated with reports of a positive programmatic impact, such as profits associated with increased demand for training and technical assistance in the components of the program. There is no similar financial incentive for university-based researchers charged with the analysis of data and reporting of results, as they are not employed by any of the organizations charged with program implementation (i.e., GISD) or future dissemination of intervention components (i.e., training and technical assistance providers).

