### Primary outcomes

#### Violence

We will use the Michigan Profile for Healthy Youth (MiPHY) to evaluate student outcomes related to aggression and violence, and the intermediate school district across Genesee Co. The MiPHY represents the Michigan Youth Risk Behavior Survey (YRBS), part of a nationwide surveying effort led by the Centers for Disease Control and Prevention (CDC) to monitor students’ health risks and behaviors (Michigan Department of Education, 2016). YRBS has been conducted annually by the CDC since 1993 and the psychometric properties have been evaluated and published (Brener et al., 2002; Kann et al., 2018). The MiPHY was designed to track students over time and those that move across districts. As a coordinated survey, MiPHY assesses a broad range of content related to students’ physical and mental health as well as attitudes, beliefs, and behaviors in their school, home, and neighborhood environments. Related to this project, it will include measurement of aggressive behavior, violence victimization, and bullying. The data will be maintained by GISD and provided in a de-identified format to the evaluation teams.

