#### School-level discipline

The School Information System (SIS) is a web-based information system, implemented in GISD schools along with PBIS. It is designed to be an efficient, reliable, and confidential tool for collecting, summarizing, and using student discipline data, enabling school personnel to be more successful decision makers. Presently, schools in Genesee Co. report student violations and truancy via SIS, creating a standardized and comparable metric across schools in the proposed study area. We will compare treatment versus control school outcomes utilizing these data. Additional time will be allocated for more intensive analyses and linkage with MiPHY and focus group results.

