### Analysis

Our primary hypothesis is that students in schools receiving the intervention will report less violence (over time) compared to students in the control group. We also hypothesize that the intervention schools have an overall lower rate of violence over the school year compared with control schools. We expect that using implementation facilitation led by a climate specialist as part of a 3-person leadership team is a feasible and sustainable approach to integrating and effectively delivering the three intervention components. Finally, we expect that students in the intervention schools will report more positive school climate compared with those in control schools and that this, in turn, will result in lower improved mental health outcomes.

A cluster randomization design is proposed with random assignment by school to one of two arms: intervention or control. Evaluation of effectiveness outcomes will involve testing at four time points: a fall of Year 1, spring of Year 1, fall of Year 2, spring of Year 2. Measures will include school records and self-report data from students and teachers. The survey of students makes use of currently collected MiPHY data. Ten schools will be recruited in the first year and 10 in the following year; staggered recruitment will allow some initial evaluation testing of the program and allow the earliest possible start time with a number of schools. Including 20 schools in the research provides an opportunity to examine school level differences. To adjust for bias introduced by multiple comparisons across our outcome variables, we will use a pair of conservative (Tukey and Bonferonni) *p*-value adjustments in addition to reporting direct effect sizes (e.g., group differences in means) to allow for assessment not dependent on standard null hypothesis testing.

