#### Behavioral outcome analysis

We will undertake comparability of the two arms (intervention and control) will be undertaken, including school size and socio-demographic indicators (e.g., proportion of free/reduced school lunches, proportion of students from various ethnic backgrounds, aggregate reports of income). Our primary analytic strategy uses mixed-effects models with full information maximum likelihood, which uses all available data for point estimation and sandwich estimator for the standard errors.

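### The rule not to collect data after discontinuation or deviation can bias the randomised comparison if it reaches the student survey or school-record outcomes

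*Protocol article*

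**What the plan says.** The sentence at issue stands in the Methods subsection of the protocol article: "We do not intend to collect data from participants who discontinue or deviate from protocols". Nothing limits it to a data source, a type of participant or a kind of deviation, and no other section provides for follow-up after discontinuation.

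The sections it bears on are these:

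- **Primary study aim:** "The primary study aim is to examine the overall effectiveness of the intervention, including change in violence", over time, "compared with a control group of students who receive school practice as usual".
- **Analysis:** "A cluster randomization design is proposed with random assignment by school to one of two arms: intervention or control". Also: "Evaluation of effectiveness outcomes will involve testing at four time points".
- **Behavioral outcome analysis:** mixed-effects models with "full information maximum likelihood, which uses all available data for point estimation".
- **Violence (primary outcomes):** "The MiPHY was designed to track students over time and those that move across districts". The same section says that the intermediate school district holds these data and passes them to the evaluators de-identified.
- **School-level discipline:** "Presently, schools in Genesee Co. report student violations and truancy via SIS".

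**The concern.** Discontinuing and deviating both happen after randomisation. A rule that stops data collection on those grounds makes the set of observed students depend on what happened during the trial, and random assignment no longer protects the comparison between arms. The control arm carries on as usual and has no restorative justice, Mental Health First Aid or environmental design delivery to depart from, so the rule could remove more people from one arm than from the other.

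The primary aim is overall effectiveness, for which results under imperfect participation are part of the answer. A later analysis plan can choose among data that exist, but it cannot restore data that were deliberately not obtained. That is why this matters in a protocol, even a condensed one.

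**Working it through.** **Inputs from the protocol article.** Schools are randomised, 10 per arm. Student surveys are planned at four waves over two school years. The rule carries no exception. The planned detectable effect is d = .27 (Power analyses, Between group analyses). The article gives no rate of discontinuation or deviation, and no outcome difference between those who leave and those who stay, so both are assumed below.

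**The scale figure first.** The d = .27 is used only as a yardstick. With J = 20 schools, m = 60 students per school, 80% power and an assumed two-sided 5% test:

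- detectable effect = (1.96 + 0.84) × √[4(ρ + (1 − ρ)/m)/J]
- at the stated ρ = .10: 0.425
- at ρ = .03, the top of the ICC range reported in the article: 0.269

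So .27 corresponds to ρ = .03 and not to the stated .10. That is a separate matter. Here it means only that percentages of .27 are rough.

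**Bias formula.** Let a share f of the intervention arm and a share g of the control arm be removed completely, and let those removed have a mean violence outcome k SD worse than those kept. The full intervention-arm mean exceeds the mean of those kept by f × k, and the full control-arm mean exceeds its own by g × k. The estimated difference therefore shifts by −(f − g) × k.

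| f | g | k (SD) | Shift (SD) | Share of .27 |
|---|---|---|---|---|
| 20% | 0 | 0.3 | −0.06 | 22% |
| 20% | 0 | 0.5 | −0.10 | 37% |
| 20% | 10% | 0.5 | −0.05 | 19% |
| 20% | 20% | any | 0 | 0 |
| any | any | 0 | 0 | 0 |

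**Effect on the test.** Take the second row, with no true effect and a nominal two-sided 5% test. The standard error is √[4(ρ + (1 − ρ)/60)/20], which is 0.096 at ρ = .03 and 0.152 at ρ = .10. The shift of 0.10 is then 1.04 or 0.66 standard errors, and the test rejects about 18% or 10% of the time.

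**What the planned model changes.** The formula assumes complete removal. Under the rule, data from waves before the event would already exist, and the likelihood model would use them. Any part of k that earlier waves predict is at least partly recovered, so the shift is smaller than shown. What remains is the part of k that observed data do not explain, because FIML is unbiased only when missingness is explained by what was observed. That condition is hard to take for granted: Table 2 lists truancy and behavioural referrals under the primary aim, and both are plausibly linked to leaving.

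**The case against.** The strongest reply is that the sentence may never touch the primary outcome. The sentence that follows it concerns data the research team gathers itself, with focus groups, interviews and surveys of teachers as examples. The student survey is an existing one held by the school district, and discipline and truancy data come from school records. On that reading the rule covers only people who leave team-run data collection. This is plausible, but the text does not say so. The lack of a stated limit is itself a reason to rewrite the sentence.

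Three further objections stand and set the limits of the point:

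- **Removal of whole schools.** A reader might infer that schools which implement poorly are dropped. The text speaks of participants and does not mention schools. The Implementation facilitation section expects tailored delivery and does not aim for full standardisation, so uneven delivery is not clearly a deviation. The Process evaluation section plans to study barriers, which fits poorly with discarding weak implementers.
- **Removal from one arm only.** A reader might infer this because controls have no intervention protocol. But the plural term used may also cover consent and data-collection procedures, which apply in both arms, and control students can discontinue too. Differential loss is possible but not established.
- **A per-protocol primary analysis.** Nothing in the article states one. The absence of a defined analysis set is commonly left to an analysis plan and is not part of this point.

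**Conclusion.** The concern holds in conditional form. As written, the rule permits avoidable missing data that depend on post-randomisation events. If it is applied to MiPHY or SIS outcomes, it can bias the school-randomised comparison, and the planned likelihood analysis repairs this only under an assumption that the rule makes harder to defend.

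A reader might go further and conclude that the rule does bias the result, and in favour of the intervention. The documents do not support that. The direction depends on those removed having worse outcomes, and the size depends on rates and differences that are nowhere given. The Background's remark that poorly implemented interventions fail makes worse outcomes plausible, but it does not establish them. The bias is zero if removal is balanced between arms or unrelated to outcome. The range of 0.06 to 0.10 SD is an upper-end illustration that rests on three assumptions: 20% removed, from the intervention arm only and completely, with outcomes 0.3 to 0.5 SD worse.

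**What to change.** Replace the sentence in the Methods subsection with a statement that:

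1. MiPHY and SIS outcomes will be obtained at every scheduled wave for all randomised schools and all consented students, whatever their adherence and whether or not they discontinue, except where consent for data use is withdrawn.
2. These outcomes will be analysed by the arm to which the school was assigned.
3. Any analysis restricted by adherence is supplementary.

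If the sentence was meant only for focus groups, interviews or teacher surveys, limit it to those sources by name. In either case, define who a participant is and what counts as a deviation.

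The cost is mainly wording. The survey is already run and held by the school district and is designed to follow students who move. The schools already report violations and truancy through SIS, and the Data linking section already provides individual codes that connect survey records across years.
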